##### Scooter skills confidence in the social environment

We will use the shortened version of the social environment scale of the Wheelchair Use Confidence Scale for manual wheelchair users [32] that was developed by Sakakibara [33] to assess scooter users’ confidence negotiating their social milieu. For this study the word wheelchair was replaced with scooter. The scale uses an 11-point scale (0 = not confident to 10 = completely confident) and a total mean score between 0 and 100 can be calculated by finding the sum of the scores of each item.

##### Scooter use and incidents

Participants will be asked to keep a diary of any scooter-related adverse events, including the following: tips or falls from the scooter, injuries to self, accidental contact with others, injuries to others, and damage to property. Participants will be asked to record the number of hours per day that they use their scooters over the course of the study.

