## Methods

### Study design

To conduct this exploratory, mixed-method, rater-blinded RCT, a two-step wedge design will be used, as illustrated in Fig. 1. With a step-wedge design, participants are randomly assigned to receive the same intervention at different times [22]. For this study, a total of 40 participants, stratified based on whether or not they have previously held an automobile driver’s license, will be randomly assigned to either the immediate intervention group or the delayed intervention group. As illustrated in Fig. 1, the immediate intervention group will receive the intervention after consent and baseline data have been collected, while the delayed group will receive the intervention after a 6-week delay. The primary endpoint of this study is at 6 weeks, so we can compare the effects of the intervention with the group who has yet to receive it.

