### Participants

For this feasibility study we plan to recruit 40 participants. As the majority of wheeled mobility users are older adults [4], the eligible community dwelling participants for this study are (1) English-speaking adults, (2) aged ≥ 60 years, (3) have one month or less combined experience of using a scooter within the past year, and (4) are able to independently transfer in and out of a scooter. We have not defined the population of interest based on their diagnoses (e.g., stroke, spinal cord injury, Parkinson’s disease), because the use of a scooter is not diagnosis specific. Individuals who have cognitive impairments that will prevent them from providing consent and from reliably completing the study questionnaires, reside in a nursing home, or plan to move outside the study intervention delivery area within the next year will be excluded.

Participants will be recruited through a variety of sources, including community healthcare units, vendors, and various seniors’ groups and seniors’ centres. Participants will be recruited through these organizations via posters, presentations, social media, and referrals. Occupational therapy staff and vendors will invite eligible clients to consider the trial.

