### Procedure

The research coordinator and principal investigator will train raters to administer all study measures. This training will include review of manuals, observations of pre-recorded mock interviews and assessments with practice scoring, practice administration with other research staff with feedback provided, and video recording of practice administration for self-reflection.

Upon enrolment, participants will be provided with a unique ID number, and the researcher will obtain written consent prior to baseline testing with all participants. The immediate intervention group will receive SCOOT after their baseline testing once or twice per week over a 6-week period (varying from 9 to 18 hours total), while the delayed intervention group will receive SCOOT 6 weeks after baseline testing. Upon completion of the intervention, all participants will be re-assessed at 6, 12, 26, and 52 weeks after randomization. Participants will also be asked not to participate in any additional training until 12 weeks have elapsed. The intervention will be discontinued upon the participant’s request, or if they are unable to continue with the research due to unforeseen events (e.g., illness).

Measures will be administered in a random order to reduce order effects. All measures, except the Wheelchair Outcome Measure (WhOM), will be collected by a blinded research assistant. The WhOM will be administered by the study therapist as this will inform the intervention. During training sessions, the therapist delivering the intervention will record any adverse effects of the intervention such as falls. As suggested by Little et al. [24], to reduce missing data, we will stress, during the consent process and whenever there is contact between participants and study personnel, the importance of collecting measurement data for the duration of the study, especially for those who discontinue the intervention.

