### Experimental intervention

SCOOT is a community-based, client-centered intervention that embeds skills training into social activities that users want to accomplish. It also uses trainer-facilitated problem solving to identify strategies to manage environmental barriers and to enable better user social participation. This intervention represents a departure from customary scooter training that is often very limited and which focuses on learning discrete skills outside of the user’s normal environment. With SCOOT, skill training (i.e., on driving, basic and advanced scooter skills) will take place during self-selected, home- or community-based activities that participants want to perform using their scooters. We will identify these activities using the WhOM [21], which identifies the most important home- and community-based activities participants wish to perform using their scooters (described below). The skills training component of the intervention is based on the scooter version of the Wheelchair Skills Training program [20].

The intervention will be held in the neighborhood of the participants, located in the Greater Vancouver Regions District of British Columbia, Canada. The intention of conducting the study within the neighborhood of the participant is to facilitate the transferability of training and to improve the ecological validity. In addition, training in the community aims to reduce participant burden of travelling to our research site, and to improve adherence. These neighborhoods are all located within an urban setting, and locations include, but are not limited to, community centers, grocery stores, and parks.

SCOOT for scooter mobility skills will be provided by occupational therapist trainers who will be trained by the principal investigator to use the same standardized approach. The therapist will keep a record of the skills that they have taught and hours of training provided. During training sessions, the therapist delivering the intervention will record any adverse effects of the intervention such as falls. We will collect data on the number of therapist visits, length of visits, therapist years of practice, years of experience working in this area, and therapist qualifications.

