### Analysis

#### Quantitative data

Data will be input into a password protected document and will be double checked for accuracy. Descriptive statistics (e.g., means, frequencies, proportions, standard deviations) and distributions and box plots will be used to display all study data. The percentage of skills taught will be calculated to determine the treatment fidelity, and the percentage of sessions attended will be calculated to determine adherence. These quantitative data will be supplemented with data from the qualitative portion of the study. We will explore the use of multiple imputation for missing outcome measure data [47]. A detailed statistical analysis plan to handle various statistical analysis issues will be created [48]. To identify covariates that will be controlled for in the larger study, we will identify factors that are strongly related to the primary and secondary outcome measures. To determine the effect size for the primary and non-count secondary outcome measures, we will perform various models, controlling for baseline scores, using an intention-to-treat analysis. That is, all participants will be included in the group to which they were allocated for purposes of analysis, whether or not they completed the intervention for that group. As this is a feasibility study, we will also calculate effect sizes based on the intervention received (e.g., on an as-treated basis). Using G*Power 3.1.0, this sample size should give us the ability to detect a large effect size of 0.46 (with α = 0.05 and power = 80%). For count data (e.g., use, accidents, and falls), we will determine the effect size by using Poisson regression [49].

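### Diary hours of scooter use do not separate training sessions, so a 6-week comparison of use can favour the immediate group with no change in participants' own use (minor, secondary outcome)

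*Protocol article*

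**What the plan says.** All references are to the protocol article.

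- **Scooter use and incidents** (under secondary outcomes) sets the measure: "Participants will be asked to record the number of hours per day that they use their scooters over the course of the study". No category of use is set apart.
- **Quantitative data** makes use an analysed outcome: "For count data (e.g., use, accidents, and falls), we will determine the effect size by using Poisson regression".
- **Procedure** gives the immediate group SCOOT "once or twice per week over a 6-week period (varying from 9 to 18 hours total"), whereas "the delayed intervention group will receive SCOOT 6 weeks after baseline testing".
- **Experimental intervention** places skills training on the scooter: it "will take place during self-selected, home- or community-based activities that participants want to perform using their scooters". The same section provides a second source of hours: "The therapist will keep a record of the skills that they have taught and hours of training provided". It does not link that record to the diary.
- **Study design** fixes the point of comparison, against the arm that is still untreated at that time: "The primary endpoint of this study is at 6 weeks, so we can compare the effects of the intervention with the group who has yet".

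**The concern.** Taken together, these sections let the training itself enter an outcome that is meant to measure its effect. A participant in the immediate group who answers the diary request literally will enter session time as scooter use. In weeks 0 to 6 a participant in the delayed group has no sessions to enter. The difference in diary hours at 6 weeks is then a mixture of sessions delivered and any change in what participants do by themselves.

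The Background section lists estimates of the intervention's effect among the aims of this feasibility study. An effect on use that contains therapist-led hours would be a poor estimate to take forward if it were read as a change in participants' own behaviour. The separation is best made when the data are collected, because a diary that holds only one daily total cannot be split afterwards from the diary alone.

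**Working it through.** **The plan's own figures.** The article gives no expected hours of use and no effect size for use. Its one power figure is a detectable effect of 0.46 with 40 participants, α = 0.05 and 80% power. It is reproduced if 0.46 is read as Cohen's f: with noncentrality 0.46² × 40 = 8.46 and 1 and 37 degrees of freedom, power is 0.81. Nothing below depends on it.

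**Inputs from the article.** Training time T is 9 to 18 h over 6 weeks, in the immediate group only. Over 6 weeks that is 9/6 = 1.5 to 18/6 = 3.0 h per week, or 9/42 = 0.21 to 18/42 = 0.43 h per day.

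**Inputs assumed, because the article does not give them.**

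- Own use B is 0.5, 1 or 2 h/day, that is 21, 42 or 84 h over 42 days. It would be the same in both groups without training.
- s is the share of session time spent on the scooter.
- d is the share of that on-scooter time that replaces trips the participant would have made anyway.

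**Formulas,** with no true effect on own use, immediate group over delayed group:

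- Total hours ratio = 1 + sT(1 − d)/B
- Non-training hours ratio = 1 − sTd/B

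**Total hours ratio:**

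| Own use B | T = 9, s = 1, d = 0 | T = 18, s = 1, d = 0 | T = 9, half | T = 18, half |
|---|---|---|---|---|
| 21 h | 30/21 = 1.43 | 39/21 = 1.86 | 25.5/21 = 1.21 | 30/21 = 1.43 |
| 42 h | 51/42 = 1.21 | 60/42 = 1.43 | 46.5/42 = 1.11 | 51/42 = 1.21 |
| 84 h | 93/84 = 1.11 | 102/84 = 1.21 | 88.5/84 = 1.05 | 93/84 = 1.11 |

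The *half* columns apply either when half the session is off the scooter (s = 0.5, d = 0) or when half of it replaces own trips (s = 1, d = 0.5). The total is the same in both cases.

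**What removing training hours does,** at B = 42 h and s = 1:

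| Replacement d | T | Total ratio | Non-training ratio |
|---|---|---|---|
| 0 | 9 | 1.21 | 42/42 = 1.00 |
| 0 | 18 | 1.43 | 42/42 = 1.00 |
| 0.5 | 9 | 46.5/42 = 1.11 | 37.5/42 = 0.89 |
| 0.5 | 18 | 51/42 = 1.21 | 33/42 = 0.79 |
| 1 | 9 | 42/42 = 1.00 | 33/42 = 0.79 |
| 1 | 18 | 42/42 = 1.00 | 24/42 = 0.57 |

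For any d between 0 and 1, the total ratio is at or above 1 and the non-training ratio is at or below 1. The two therefore bracket the true value, and their distance apart is sT/B. The same ordering holds if own use really does change, because session time is either added to own trips or taken out of them.

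**The case against.** **The article does not say that training hours are counted.** This stands. Inclusion follows from wording that sets no limit, not from a stated rule. The diary is a named form (Scooter Use Incidents Diary, in the legend to Fig. 1) whose instructions are not shown, and the article promises a detailed statistical analysis plan. A reader might infer that the diary is known to include all 9 to 18 hours; the text does not establish that. What remains is that the outcome as defined overlaps with the intervention, and following it literally puts session time into one arm.

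**The 6-week window for use is inferred.** Also correct. Diary hours are collected throughout the study, and the sentence on Poisson regression names no window. Totals that run past the delayed group's training contain sessions in both arms. The problem concerns the 6-week comparison, which is the between-group contrast that Study design sets out.

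**Nine to 18 hours is an upper bound.** Correct. It is training time, and sessions also include problem solving that need not take place on the scooter.

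**Subtracting training hours errs in the other direction.** This is the strongest point, and it stands against subtraction alone. Sessions are built around activities participants want to do, so some replacement of own trips is likely. At 42 h of own use, 18 h of training and half replacement, total hours give 1.21 and non-training hours 0.79. Deducting the therapist's logged hours from an unmarked diary could also remove time the participant never entered.

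**Significance.** A reader might infer an inflated false-positive rate for use. The documents give no spread of hours from which to calculate one, and they state an effect size as the aim for use, not a test. No rejection rate is claimed here.

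**Conclusion.** The point holds as a minor one. As written, a 6-week comparison of diary hours can show more use in the immediate group without any change in participants' own use. With every session hour on the scooter and no own trips replaced, the ratio reaches 1.43–1.86, 1.21–1.43 or 1.11–1.21 at an assumed 0.5, 1 or 2 h/day. The excess is smaller with partial replacement or off-scooter time, and it vanishes if training fully replaces own trips. These sizes rest on assumed own use, on literal completion of the diary, and on use being compared at 6 weeks.

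A reader might go further and conclude that the trial's effect estimates, or the case for the larger trial, are compromised. The documents do not support that. Use is one secondary outcome in a feasibility study, the primary outcome is perceived skill capacity, and the Discussion does not name scooter hours as a target of the larger trial.

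**What to change.** 1. Have the diary mark hours spent in training sessions separately from other hours on the scooter, and check the marked hours against the therapist's record.
2. For the 6-week comparison, estimate the effect on hours outside training sessions and report it beside the effect on total hours. Do not interpret the total-hours effect as a change in own use.
3. State that non-training hours may understate use when training replaces own trips, so that the two estimates bracket the effect.
4. Keep total hours as the exposure for incidents, because incidents during training are recorded too.

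The cost is one extra diary entry on training days, a match with a record the therapist already keeps, and a few sentences in the outcome definition and analysis plan. The reported effect on use is likely to be less favourable. Diaries already completed without the mark could be split only approximately, from the therapist's record.

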#### Descriptive measures and covariates (body function, health, environmental, and personal factors)

Descriptive data will be collected that includes participants’ socio-demographic characteristics (age, sex, income level of education, ethnic origin, language, marital status, type of dwelling, diagnoses, duration of functional problems, previous experience driving vehicle(s), and amount of formal care-giving received, if any). Although randomization should control for differences between the treatment groups, we will collect data on the following constructs that could affect scooter-user outcomes and which will provide additional descriptive information. The data then may be used as covariates, if there are important differences between the groups at baseline.

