**Methods:**

This feasibility study will use a mixed-methods, rater-blinded, randomized control trial, with a two-step wedge design. The study has two arms: an immediate intervention group, which will receive the intervention directly after baseline assessments, and a delayed intervention group, which will receive the intervention after a 6-week period. Forty participants, who will be stratified based on whether or not participants have previously held a driver’s license, will be randomly assigned to each arm. The intervention for this study consists of 6 weeks of one-to-one scooter training by an experienced occupational therapist, who will provide training once or twice per week over the 6 weeks. The primary outcome measure is subjective scooter skills, measured using the Wheelchair Skills Test for scooters. Secondary outcomes include objective scooter skills, confidence, mobility, and satisfaction with selected participation activities. Descriptive measures include cognitive status, functional status, hearing, vision, physical accessibility of the home and community, and visual attention and task switching. Qualitative interviews will be conducted with the first ten willing participants from each group to learn about their scooter use and experiences with SCOOT.

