### Randomization

The allocation of each participant will be communicated to the study research coordinator after baseline data and consent have been obtained. The allocations will be managed by the study statistician using an auditable computer program and a 1:1 allocation ratio within each stratum. Blocking sizes will not be revealed until needed for analysis.

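### Covariates may enter the effect models when the arms look different at baseline, an undefined trigger that chance would often trip; fix the model in advance, with the licence stratum in it

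*Protocol article*

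**What the plan says.** All references are to the protocol article.

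- **Study design** and **Randomization**: "a total of 40 participants, stratified based on whether or not they have previously held an automobile driver’s license" are to be randomized, "using an auditable computer program and a 1:1 allocation ratio within each stratum". No reason is given for choosing licence history as the stratification factor.
- **Quantitative data** (under Analysis): for the primary and non-count secondary outcomes, "we will perform various models, controlling for baseline scores, using an intention-to-treat analysis". Baseline score is the only covariate named. The same section promises a detailed statistical analysis plan. It also says, for the later larger trial, that covariates will be chosen by how strongly they relate to the outcomes.
- **Descriptive measures and covariates**: after granting that randomization should take care of group differences, the article lists further constructs thought capable of affecting outcome and adds: "The data then may be used as covariates, if there are important differences between the groups at baseline". It gives no threshold, no final list of covariates and no restriction to a sensitivity analysis.

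**The concern.** The baseline-difference trigger is the only rule the article states for adding covariates to this trial's own comparison, and it uses the wrong criterion. Under sound randomization an observed difference between arms is chance. Its size does not show how strongly a covariate predicts the outcome, which is what makes adjustment useful. The trigger also leaves the model open until the groups have been seen, so the reported effect size depends on which differences happened to arise and on someone's view of what is important.

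The article uses the better criterion, relation to outcome, only for choosing covariates for the next trial.

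This matters even in a feasibility study. The last paragraph of the Background lists estimates of the intervention effect and their variances among the study's outputs, and these are meant to inform a larger trial.

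A smaller, related point is that the stratification factor is not mentioned for the effect models. If licence history predicts scooter skill, a model without it leaves that variation in the error term. The reported standard error is then larger than the stratified design warrants.

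**Working it through.** **1. The plan's own figure.** The article says "this sample size should give us the ability to detect a large effect size of 0.46", with alpha 0.05 and 80% power. The index is not named, so I read it as Cohen's f in a two-group analysis of covariance with N = 40 and one covariate (baseline score).

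- Noncentrality = f² × N = 0.46² × 40 = 8.464.
- Degrees of freedom: 1 and 40 − 2 − 1 = 37.
- Power = 0.809, and the smallest f detectable at 80% power is 0.455. The figure reproduces.

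**2. Cost of adding the licence stratum.** The denominator degrees of freedom fall from 37 to 36. If the stratum explains nothing, power is 0.808, the smallest detectable f is still 0.455, and the N needed for f = 0.46 is still 40.

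**3. Possible gain from the stratum (assumed strengths).** If the stratum explains a share R² of the residual variance, the reported standard error is multiplied by √(1 − R²), the effective f becomes 0.46/√(1 − R²), and the equivalent sample size is 40/(1 − R²).

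| Assumed R² | SE ratio | Equivalent N | Power |
|---|---|---|---|
| 0.05 | √0.95 = 0.975 | 40/0.95 = 42 | 0.828 |
| 0.10 | √0.90 = 0.949 | 40/0.90 = 44 | 0.847 |
| 0.15 | √0.85 = 0.922 | 40/0.85 = 47 | not computed |
| 0.20 | √0.80 = 0.894 | 40/0.80 = 50 | 0.886 |

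**4. How often chance trips the trigger.** Seven constructs follow the rule: cognition, function, hearing, scooter characteristics, accessibility, visual attention and task switching, and visual acuity. The article does not define the trigger, so I tried three definitions, taking the constructs as independent. With 20 per arm, a standardized mean difference has a standard deviation of √(2/20) = 0.316.

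| Meaning given to *important* | Chance for one construct | At least one of 7 |
|---|---|---|
| p < 0.05 | 0.05 | 1 − 0.95⁷ = 0.302 |
| Standardized difference > 0.5 | 0.114 | 1 − 0.886⁷ = 0.57 |
| Standardized difference > 0.25 | 0.429 | 1 − 0.571⁷ = 0.98 |

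If socio-demographic items also count and there were, say, 15 candidates, the p < 0.05 version gives 1 − 0.95¹⁵ = 0.54.

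**5. Direction of the harm.** I used a simulation of 20,000 trials per setting. Its assumptions are not in the article: N = 40, 70% licensed, seven independent covariates each with coefficient 0.3, residual SD 1, and selection when the standardized difference exceeds 0.25. Rejection rates under no treatment effect, at nominal 0.05:

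| Licence effect (SD) | Baseline only | Baseline + stratum | Baseline + covariates picked by imbalance, no stratum |
|---|---|---|---|
| 0 | 0.049 | 0.049 | 0.032 |
| 0.5 | 0.047 | 0.051 | 0.030 |
| 1.0 | 0.038 | 0.049 | 0.024 |
| 1.5 | 0.026 | 0.049 | 0.016 |

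None of the departures from 0.05 is upward. With a true difference of 0.92, power across the four rows is 0.59, 0.58, 0.54 and 0.48 for baseline only, about 0.59 throughout with the stratum, and 0.60, 0.59, 0.53 and 0.47 with picked covariates. These values lie below 0.80 because the simulated covariates add outcome variance; only comparisons between columns are meaningful.

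At a licence effect of 1.5 SD under no treatment effect, the estimate itself varies equally with or without the stratum (SD 0.410 and 0.408). Stratified allocation has already balanced licence history. Leaving it out makes the reported standard error too large rather than the estimate noisier.

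**The case against.** **The stratum may simply be left to the analysis plan.** A reader might infer that the protocol excludes the stratum from the model. The text does not support that. It names baseline scores without saying that nothing else will be used, it promises a detailed analysis plan, and a condensed article often leaves this detail out. This objection stands, so the stratum belongs in the remedy and is not charged as an error. It does not reach the baseline-difference trigger, which the article states outright and which a later plan would inherit.

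**The candidates were already screened.** The article introduces them as constructs that could affect outcome, so the trigger is a second filter on a plausible list, and its wording is permissive. This is fair, and it weakens any claim that adjustment would be spent on irrelevant variables. It does not make imbalance a sound way to choose among them, and a permissive rule without a threshold leaves the model more open.

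**The study is exploratory.** Its stated hypotheses concern feasibility, and no confirmatory claim rests on one locked model. This limits the severity. Effect and variance estimates are nevertheless stated outputs.

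**The sizes are assumed.** The article gives neither the share of licensed participants nor the strength of licence history as a predictor, and it does not define the trigger. This stands, and the figures above are illustrations.

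**Conclusion.** The point holds as an inexpensive improvement of moderate weight. The firm part is the written trigger: it is undefined, it depends on the data, and chance alone would trip it in roughly 30% to 98% of trials across the definitions tried, with seven independent constructs assumed. The licence stratum is a secondary part, because the unseen analysis plan may already include it.

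Three stronger readings should be resisted.

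- A reader might infer inflated false positives. The simulation shows rejection rates at or below nominal when the trigger is applied as written, to baseline differences alone. The harm is intervals that are too wide, precision understated or lost, and an effect estimate that is not fixed in advance.
- A reader might infer that the protocol regards licence history as prognostic. It gives no reason for stratifying on it, so the gain from including it (a standard error 2.5% to 8% smaller for R² of 0.05 to 0.15) rests on an assumption.
- A reader might take this as a challenge to the sample size. It is not one: 0.46 reproduces as Cohen's f with 40 participants in total.

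**What to change.** - In the section on descriptive measures and covariates, delete the sentence that lets measures become covariates because of baseline differences. Report those differences descriptively.
- In the analysis section or the statistical analysis plan, prespecify the 6-week model for each non-count outcome: outcome on allocated group, baseline score and licence stratum.
- Name any further covariate in advance on prognostic grounds, before the arms are compared, or confine it to a sensitivity analysis labelled as such. The article's plan to identify covariates for the larger trial by their relation to outcome can stay as it is.

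The cost is a change of wording and one degree of freedom. Licence status is known at randomization, so no new data are needed.
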